#### Data Collection and Analysis Plan

This study adopts a single-group pretest-posttest design implemented across 2 instructional cycles (first and second semesters). Quantitative data will be gathered with the AEIS—a validated 26-item instrument covering 4 subscales: emotion awareness (items 1-7), emotional expression (items 8-12), emotion regulation (items 13-17), and emotional use (items 18-26). Each item is scored on a 4-point Likert scale (ranging from 0=strongly disagree to 3=strongly agree); higher scores denote greater EI [22]. Permission to use the AEIS has been obtained from the original author. The scale will be administered in week 3 (pretest evaluation) and week 16 (posttest evaluation) of each semester. Qualitative data will consist of students’ reflective reports—collected throughout both cycles—and classroom observations conducted in week 17 to document behavioral engagement during gameplay and AI-patient interactions.

At the item level, AEIS subscale scores will be prorated when no more than 1 item per subscale is missing; otherwise, the subscale will be set to missing. At the record level, patterns of missingness will be inspected with the Little MCAR test [23]. As linear mixed effects models (LMMs) provide unbiased estimates under a missing-at-random assumption, incomplete cases will be retained in the primary analyses. For ancillary paired sample 2-tailed *t* tests or Wilcoxon signed-rank tests, missing posttest values will be multiply imputed (20 imputations using predictive mean matching); the imputed results will be pooled following the rules formulated by Rubin [23] and compared with complete-case outputs as a sensitivity check.

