Descriptive statistics (means and SDs or medians and IQRs) will be reported for all variables. The normality of pretest-posttest difference scores will be checked with the Shapiro-Wilk test. If the distribution is normal, within-participant changes in AEIS total and subscale scores will be analyzed with paired sample 2-tailed *t* tests; otherwise, the Wilcoxon signed rank test will be used. Effect sizes will be expressed as Cohen *d* with 95% CIs. To compare change trajectories between cycles, an LMM with random intercepts for participants will be fitted, including fixed effects for time (before the intervention vs after the intervention), cycle (1 vs 2), and their interaction (time × cycle). Holm-Bonferroni adjustment will control the family-wise error rate across AEIS subscales. All analyses will follow an intention-to-treat principle (participants with ≥1 posttest record retained); sensitivity checks with complete-case data will evaluate robustness. Statistical significance is set at α=.05 (2-tailed). Analyses will be conducted in SPSS software (version 29.0; IBM Corp) and R (version 4.4.0; R Foundation for Statistical Computing; *lme4* package for LMMs).

To capture students’ experiences and perspectives, we collected qualitative data through structured reflective reports and oral and written feedback after the implementation of the innovative teaching practices. Each student was required to complete a reflective report structured around 5 open-ended questions aligned with the core learning domains of self-awareness, emotional self-awareness, social awareness, empathic communication, and crisis management competence; for example, students described personal insights gained from participating in the card-based educational game, emotional reactions experienced during gameplay, and strategies for recognizing and responding to peers’ emotional cues. They also reflected on their ability to demonstrate empathy in simulated dialogues with AI virtual patients and articulated how these experiences contributed to their confidence in managing psychological crises. Each reflective entry was expected to exceed 100 Chinese characters, thereby encouraging deeper engagement and detailed narrative accounts of their learning processes.

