#### Cycle 2: Sampling and Recruitment

This cycle will be conducted during the second semester (spring term) of the third year for a new cohort of nursing students. On the basis of the results, feedback, and reflective evaluations gathered from faculty and students during the first cycle, the instructional content and design of the GBL activities and AI virtual human interactions will be refined. The revised intervention will then be implemented as part of a second action research cycle, with the aim of enhancing the overall effectiveness of the innovative teaching approach and achieving the study’s educational objectives.

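### The intention-to-treat set, defined by having a posttest record, drops the pretest-only students whom the missing-data rules keep and impute

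*Protocol article*

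**What the plan says.** All of the following is in the protocol article. Four statements are in Data Collection and Analysis Plan; the other two places are named.

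- **Measurement schedule:** "The scale will be administered in week 3 (pretest evaluation) and week 16 (posttest evaluation) of each semester".
- **Cohorts:** "This cycle will be conducted during the second semester (spring term) of the third year for a new cohort of nursing students" (under the heading Cycle 2: Sampling and Recruitment). Together with the schedule, this gives each student at most one pretest and one posttest. The Phase 3 schedule puts the posttest in weeks 18 and 36 instead of week 16, but that is still one per student.
- **LMM:** on the ground that the model is unbiased when data are missing at random (MAR), "incomplete cases will be retained in the primary analyses".
- **Paired tests:** "missing posttest values will be multiply imputed (20 imputations using predictive mean matching"), and the pooled results are "compared with complete-case outputs as a sensitivity check".
- **Analysis set:** the next paragraph sets one rule for everything: "All analyses will follow an intention-to-treat principle (participants with ≥1 posttest record retained); sensitivity checks with complete-case data will evaluate robustness".
- **Attrition** (Sample Size and Power Analysis): 15% to 20%, with 40 recruited per cycle to leave 32 completers.

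**The concern.** A rule requiring at least one post-baseline record is useful in a trial with several follow-up visits, because it keeps people who missed some of them. With a single follow-up it selects those who reached it. Applied to all analyses, the parenthesis removes the students for whom the missing-data paragraph was written.

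Three things are at stake. The headline change would be a completer estimate labelled intention-to-treat. The complete-case comparison would be reported as a robustness check although it cannot show the effect of dropout. And two analysts could each follow the protocol and reach different estimates, with the choice still open after the data are seen. There is no control arm in which a similar attrition bias might offset this one.

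**Working it through.** **1. The plan's own figures.** For a paired comparison with d = 0.50, two-sided α = .05 and power .80, the normal approximation gives ((1.960 + 0.842)/0.5)² = 31.4, rounded up to 32. (The noncentral t calculation gives 34, with power 0.782 at 32; this does not bear on the present point.) Allowing for attrition, 32/0.80 = 40 and 32/0.85 = 37.6, so 38. The plan's 32 and 40 are reproduced, and 32 is a number of completers.

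**2. Who is in each set, per cycle.**

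| | 15% attrition | 20% attrition |
|---|---|---|
| Enrolled | 40 | 40 |
| Pretest only | 6 | 8 |
| Kept under the missing-data paragraph | 40 | 40 |
| Kept under the posttest-record rule | 34 | 32 |

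Over two cycles at 20% attrition, the LMM uses 80 pretests + 64 posttests = 144 records under the first rule and 64 + 64 = 128 under the second. For the 37 students already enrolled in cycle 1, 37 × 0.85 = 31.5 and 37 × 0.80 = 29.6, so about 6 or 7 students are at issue.

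**3. What the complete-case check can show.** The planned model (time, cycle, interaction, random intercept) was fitted to one simulated data set of 80 students. The 16 with the lowest baselines (8 per cycle) had no posttest. The time effect, which is the cycle 1 change, was 6.38 points with everyone kept. It was 4.51 under the posttest-record rule and 4.51 in complete cases. The last two are equal because they use the same 64 students. This shows only that the check is blind to dropout. A single data set (simulated true change 5 points) says nothing about the size of bias.

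**4. Possible size of the bias.** The documents do not give the pre-post correlation r or the dropout mechanism, so both are assumed. Let the pretest and posttest have equal SD, let dropout depend on the pretest alone, and let s be the shift in the completers' mean pretest, in SD units. The slope of the change score on the pretest is r − 1, so

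bias in completers' mean change = −(1 − r) × s.

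With 20% dropout and a log-odds slope of 1 per SD, s is about 0.17 in absolute value. The size of the bias is then:

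- r = 0.4: 0.6 × 0.17 = 0.10 SD
- r = 0.5: 0.5 × 0.17 = 0.09 SD
- r = 0.7: 0.3 × 0.17 = 0.05 SD

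A simulation with 400,000 students agrees. At r = 0.5 and a true change of 0.500 SD, completers gave 0.414 when low scorers dropped out and 0.587 when high scorers did. An estimate regressing posttest on pretest and averaging over all pretests gave 0.501 and 0.500. At 15% dropout the completer values were 0.433 and 0.567.

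If dropout is unrelated to the scores, s = 0 and the bias is zero.

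**5. Scale.** At r = 0.5 the SD of the change is √(2 × 0.5) = 1, so the standard error with 32 completers is 1/√32 = 0.18 SD. A bias of 0.09 SD is about half of that.

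**The case against.** The strongest reply is that the parenthesis says who is retained and does not say that others are excluded. The missing-data paragraph is the more specific text: it names the model, the assumption, the number of imputations and a comparison with complete cases. If it governs, dropouts are handled and that comparison is informative. This reading is possible. But the parenthesis stands as the definition of the set for all analyses, and excluding the rest is the more natural reading. The harm depends on that reading; the conflict between the two texts does not.

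Four further limits on the point stand.

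- **A reader might infer that nothing is left to impute.** The documents do not support that. A subscale is set to missing when more than one of its items is unanswered, so a submitted posttest can still have gaps. Only the handling of whole-record dropout is cancelled.
- **A reader might infer that the main set and the complete-case set are identical.** They coincide for dropouts. A student who enrols but misses the pretest and completes the posttest is in the first set and not the second, and missing subscales can also separate them.
- **The size is conditional.** Nothing in the documents supports a log-odds slope of 1 per SD, which is a strong dependence.
- **The repair does not remove all attrition bias.** If dropouts would have changed differently for reasons the pretest does not explain, neither the LMM nor imputation from the pretest corrects it.

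It can also be said that the study is uncontrolled and its limitations section already restricts causal claims. That lowers the stakes but does not reconcile the two rules.

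**Conclusion.** The contradiction is real and can be seen in consecutive paragraphs of one section. With one posttest per student, the analysis-set rule, read literally, leaves out the 6 to 8 of 40 students per cycle whom the plan otherwise keeps and imputes. For those students the missing-data handling is void and the complete-case check is uninformative.

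The resulting bias in mean change runs from zero (dropout completely at random) to about 0.05 to 0.10 SD in either direction. The upper range assumes 20% dropout, log-odds ±1 per SD of baseline AEIS and r from 0.4 to 0.7. A MAR analysis that uses the pretest-only records removes this bias; bias from dropout that the pretest does not explain would remain.

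The documents do not show that the result will be biased, only that the plan as worded could neither correct nor detect such a bias. Nor does the point show that the study is too small: the sample size is unaffected, since 32 is already a completer number.

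**What to change.** Replace the parenthesis with a rule of this kind: *all enrolled, consenting participants with at least one AEIS record (pretest or posttest) are included in the LMM*. Keep the multiple imputation for students with a pretest but no posttest in the paired tests. Define the sensitivity set separately, as students with both records.

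If a completer set is what the investigators want, call it that, and delete the statements that incomplete cases are retained and missing posttests imputed.

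Either route costs a wording change and needs no new data, students or sample size calculation. It should be settled before the final analysis after week 36, and preferably before the preliminary analysis at the end of cycle 1.

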### Sample Size and Power Analysis

Using G*Power 3.1 (Heinrich Heine University) for a paired sample 2-tailed *t* test (“Means: difference between two dependent means, matched pairs”), we set α=.05, desired power=.80, and a medium anticipated effect size of Cohen *d*=0.50—consistent with meta-analytic estimates for short educational interventions targeting EI. The calculation yielded a required completer sample of 32 students to detect the pretest-posttest difference with 80% power. Allowing for typical nursing-course attrition of 15% to 20%, we plan to recruit 40 participants per cycle, ensuring that at least 32 remain for posttest analysis.

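### The complete-case robustness check cannot show dropout that depends on the unseen posttest, and the stated analysis set makes it close to a tautology

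*Protocol article*

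**What the plan says.** All references are to the Protocol article.

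- **Missing data** (Data Collection and Analysis Plan): "As linear mixed effects models (LMMs) provide unbiased estimates under a missing-at-random assumption, incomplete cases will be retained in the primary analyses". For the ancillary paired tests, missing posttests are imputed 20 times by predictive mean matching (PMM), and the pooled result is "compared with complete-case outputs as a sensitivity check". Little's MCAR test is the only diagnostic of missingness.
- **Testing and models** (next paragraph of the same section): all analyses are called intention-to-treat, but the set is limited to students with at least one posttest record. The paragraph then adds that "sensitivity checks with complete-case data will evaluate robustness".
- **Measurements**: the Adult Emotional Intelligence Scale (AEIS) is given once before and once after the intervention in each semester. The Cycle 2 section says that the second semester uses a new cohort, so no student has more than one posttest.
- **Expected loss** (Sample Size and Power Analysis): a "required completer sample of 32 students", an allowance for "typical nursing-course attrition of 15% to 20" per cent, and "we plan to recruit 40 participants per cycle".
- **Design** (Strengths and Limitations): a single group with no control arm.

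**The concern.** A robustness check should relax the assumption on which the main analysis depends. Here the main analysis assumes that a leaver would have changed like stayers with the same pretest score. The check assumes more than that: for the mean change, leavers would have changed like stayers overall. Agreement between the two says little about whether the weaker assumption is true.

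The design is exposed to this. A leaver contributes a pretest and nothing else on the AEIS. Without a control arm, the pre-post change is the effect estimate, so any difference between leavers and stayers that the pretest does not explain enters it directly.

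The analysis-set rule adds a separate problem. With one posttest per student, requiring a posttest removes the very students whom the preceding paragraph says will be retained or imputed. Under that rule the mixed model and the complete-case analysis use nearly the same data.

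**Working it through.** **1. The plan's own figures.** Inputs from Sample Size and Power Analysis: two-sided α = 0.05, power 0.80, d = 0.50.

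- Completers, normal approximation: ((1.960 + 0.842)/0.50)² = 31.4, rounded up to 32. This matches. The noncentral t gives 34, with power 0.782 at n = 32; that small gap is not the issue here.
- Enrolment: 32/0.80 = 40 and 32/0.85 = 37.6, rounded up to 38. The planned 40 matches the 20% allowance.
- Expected leavers out of 40: 0.15 × 40 = 6 and 0.20 × 40 = 8.

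**2. What each analysis assumes about a leaver.**

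| Analysis | Assumption |
|---|---|
| Mixed model, pretest-only students kept | Missing at random: same expected change as stayers with the same pretest |
| PMM imputation (no shift stated) | The same |
| Complete-case mean change | Stricter: leaving unrelated to change |
| Little's MCAR test | Sees only observed scores, in effect the pretest |

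No row allows a leaver to differ from stayers with the same pretest.

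**3. Can the methods disagree?** I simulated one cohort of 40 with 20% leaving, SD of change 1, true change 0.50 and 1,500 runs. The mixed model had a random intercept and kept pretest-only students; PMM used 20 imputations from the pretest. The pre-post correlation and the dropout mechanisms are assumptions, since the article gives none. Simulation error is about (1/√32)/√1500 = 0.005.

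| Reason for leaving | Correlation | Complete-case | Mixed model | PMM |
|---|---|---|---|---|
| Chance | 0.5 | 0.49 | 0.49 | 0.49 |
| High pretest | 0.5 | 0.63 | 0.50 | 0.47 |
| Low pretest | 0.5 | 0.39 | 0.51 | 0.55 |
| Low posttest given pretest (unseen) | 0.5 | 0.71 | 0.71 | 0.71 |
| Low posttest given pretest (unseen) | 0.7 | 0.72 | 0.72 | 0.72 |
| Low change (unseen) | 0.5 | 0.75 | 0.70 | 0.68 |
| Low change (unseen) | 0.7 | 0.74 | 0.71 | 0.69 |

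When leaving depends on the pretest, the comparison works: 0.63 against 0.50 would be noticed. When it depends on the posttest given the pretest, all three are about 0.21 to 0.22 too high and agree. When it depends on the change itself, all are about 0.18 to 0.25 too high and separate by only 0.05 to 0.07.

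**4. The analysis-set rule.** In one simulated data set of 40 with 8 leavers:

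- mixed model on students with a posttest: 0.3894, SE 0.1709
- paired difference in completers: 0.3894, SE 0.1709
- mixed model with pretest-only students kept: 0.3677, SE 0.1659

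Under the posttest rule the first two coincide. They could differ only through missing pretests or items.

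**5. Illustrative size.** All-enrolled change = (1 − q) × 0.50 + q × m, where q is the fraction lost and m is the leavers' change (assumed):

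| m (SD) | q = 0.15 | q = 0.20 |
|---|---|---|
| +0.75 | 0.425 + 0.1125 = 0.54 | 0.40 + 0.15 = 0.55 |
| +0.25 | 0.425 + 0.0375 = 0.46 | 0.40 + 0.05 = 0.45 |
| 0 | 0.425 | 0.40 |
| −0.25 | 0.425 − 0.0375 = 0.39 | 0.40 − 0.05 = 0.35 |

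These depend on the fraction lost, not on whether a cycle enrols 40 or the 37 reported for cycle 1.

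**The case against.** The strongest reply is that no missing-at-random method can detect dropout that depends on unseen data. That is a general limit and not an error of this plan. The article states its assumption openly, never claims to test departures from it, and a tipping-point analysis is the kind of detail that a separate analysis plan often holds. This stands in part: the mere absence of such an analysis would be no finding. But the article does fix its missing-data methods and assigns the complete-case comparison the task of evaluating robustness. That assignment is the weak choice. The conflict between the two paragraphs is in the text itself.

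Three stronger readings are tempting, and the documents do not support them.

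- A reader might infer that the planned methods must always agree. If pretest-only students are kept, they diverge when leaving depends on the pretest, and Little's test may pick that up too.
- A reader might infer that dropout will inflate the result. The Introduction links academic and internship pressure to distress and burnout, but it does not link either to leaving the course or missing the posttest. The attrition figure comes without reasons. Bias in either direction is possible.
- A reader might take the illustrated gaps as estimates. They rest on leaver changes for which the article gives no source.

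**Conclusion.** The point holds in a limited form. As fixed, the complete-case comparison can reveal dropout related to the observed pretest, but not dropout related to the posttest or change that was never seen. If the posttest-record rule governs, the comparison with the mixed model is close to empty, because both use nearly the same students; that rule also contradicts the paragraph that retains and imputes incomplete cases.

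At the attrition that the article allows for, a completer change of 0.50 SD would exceed the all-enrolled change by 0.075 to 0.10 SD if leavers did not change, and by about 0.11 to 0.15 SD if they fell by 0.25 SD. It would fall short if leavers would have gained more than stayers. These sizes depend wholly on the assumed leaver change. The conclusion that the check is blind to this kind of dropout does not. It should be settled before the posttest data are analysed.

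**What to change.** 1. **Use one analysis set.** Define it as all enrolled students with a pretest, and replace the posttest-record rule, so that the two paragraphs agree. Without this step no leavers remain to impute or shift.
2. **Keep the mixed model, PMM and complete-case analyses, but move the robustness statement.** Base it on a delta-adjusted version of the same 20 imputations: set leavers' mean change to zero, then shift it in steps, and report the shift at which the AEIS total result is no longer significant. Describe the complete-case comparison as a check on pretest-related dropout only.
3. **Optional.** Add early-course Virti use and reflection-log counts to the imputation model. Limit them to weeks observed for nearly all students, because leaving itself cuts these counts short and PMM cannot extrapolate beyond its donors. With 6 to 8 leavers and about 32 completers, use few such variables.

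The cost is a few sentences in the plan, slightly more analysis work and no new data collection. The downside is that the robustness statement may read less favourably.

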In addition to written reflections, student oral and written feedback were gathered during debriefing sessions immediately after the teaching interventions. These interactive discussions invited participants to share their impressions of the AI virtual patient encounters and the gamified learning with card play, highlighting both challenges and perceived benefits. Students frequently commented on the authenticity of the AI-driven dialogues, which prompted them to practice empathic responses, and on the playfulness of the card game, which fostered self-discovery and peer interaction. Oral and written feedback not only provided spontaneous, unstructured accounts but also allowed for triangulation with the reflective reports, offering complementary insights into how the innovative teaching strategies shaped EI and learning engagement. Together, these qualitative materials provided a rich and multifaceted dataset for thematic analysis, illuminating both individual developmental trajectories and collective learning dynamics within the cohort.

During the practical sessions with AI virtual patients, investigators used structured observation rubrics to evaluate student performance across five domains: (1) the ability to recognize the patient, introduce themselves, and demonstrate proactive caring; (2) the use of appropriate communication skills during interviews or technical procedures; (3) the demonstration of empathy in patient interactions; (4) the accuracy of relevant assessments such as symptom evaluation or suicide risk assessment; and (5) the quality of group reflective sharing after practice. Each domain was equally weighted at 20 points, for a total of 100 points in the rubric.

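### As described, the individual reflective report leans toward benefit and has no topic on what failed or did not change, and the Methods state favourable student comments ahead of the analysis

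*Protocol article*

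**What the plan says.** Under Data Collection and Analysis Plan, each student completes "a reflective report structured around 5 open-ended questions aligned with the core learning domains". The article illustrates the content with five items: "students described personal insights gained from participating in the card-based educational game"; "emotional reactions experienced during gameplay"; "strategies for recognizing and responding to" the emotional cues of peers; "They also reflected on their ability to demonstrate empathy in simulated dialogues with AI virtual patients"; and finally that students "articulated how these experiences contributed to their confidence in managing psychological crises".

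The same section describes oral and written feedback at debriefings, which brought out difficulties as well as benefits. It then reports, in the past tense, that "Students frequently commented on the authenticity of the AI-driven dialogues, which prompted them to practice empathic responses", and that the card game led to self-discovery and interaction among peers. A structured rubric for observed performance follows. Reports, feedback and observation notes are all to be analysed thematically and set beside the AEIS results to explain the changes seen.

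Under Cycle 2: Sampling and Recruitment, the course is to be revised "On the basis of the results, feedback, and reflective evaluations gathered from faculty and students during the first cycle". The Results section adds an expert panel meeting between the cycles.

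**The concern.** The reports have two jobs. They help to explain any change in AEIS, and they are one of the inputs to the revision before cycle 2. Both jobs need accounts of no effect or of a bad experience as much as accounts of benefit.

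A topic that asks how the course contributed to confidence tends to draw out a contribution, whether or not the student felt one. If such accounts are then set beside a rise in AEIS, part of their agreement comes from the way the question was put. There is no control group to offset this, as Strengths and Limitations acknowledges.

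The favourable statements in the Methods add a second problem. They describe effects on students before the planned coding has been done, which risks settling the themes in advance.

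**Working it through.** The plan gives no figure for this point and no formula applies. The check is a reading of the text in four steps.

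**1. Classify the five described topics (Data Collection and Analysis Plan).** Each lines up with one of the five learning domains that the section names. The pairing is my reading.

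- Self-awareness: "students described personal insights gained from participating in the card-based educational game". Presupposes a gain.
- Emotional self-awareness: "emotional reactions experienced during gameplay". Neutral, since a reaction can be unpleasant.
- Social awareness: "strategies for recognizing and responding to" peers' cues. Neutral, and does not evaluate the teaching.
- Empathic communication: "They also reflected on their ability to demonstrate empathy in simulated dialogues with AI virtual patients". Neutral, since a student may report low ability.
- Crisis management: "articulated how these experiences contributed to their confidence in managing psychological crises". Presupposes a positive contribution.

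Count: 2 presuppose benefit, 3 are neutral (2 + 3 = 5), and 0 ask about failure, absence of change or what to alter.

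**2. Look for other routes for negative information.**

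- Debriefing feedback, both oral and written, covers challenges and is unstructured.
- The observation rubric has five domains of 20 points each (5 × 20 = 100) and can return low scores.
- The revision draws on faculty as well as students (Cycle 2: Sampling and Recruitment) and on expert feedback (Results).

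Negative information can therefore reach cycle 2. What is lacking, on the description given, is a place in the individual structured report that asks for it.

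**3. Find where the other measures help least.** The AEIS has four subscales: awareness, expression, regulation and use of emotion (7 + 5 + 5 + 9 = 26 items). None covers crisis management, yet crisis management is the second objective under Aim. The rubric does score the accuracy of assessments such as suicide risk, but that is observed performance and not the student's own view of competence. For that view, the described report topic is the structured source, and it is one of the two that presuppose benefit.

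**4. Check the order of events.** The Abstract says that cycle 1 has begun, with 37 students enrolled, and that posttest AEIS results are still to be collected. The thematic analysis is written in the future tense. The statement "Students frequently commented on the authenticity of the AI-driven dialogues, which prompted them to practice empathic responses" and the one on the card game are in the past tense within the Methods. Although the debriefings are said to cover difficulties too, the comments actually reported are favourable. They are not labelled as preliminary.

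**The case against.** **The question wording is not shown.** The five items follow a phrase marking them as examples, and they describe what students wrote, not what they were asked. A condensed article may leave the questions to a fuller document. This stands as a limit: the conclusion covers the topics as described. It does not remove the point, because the five examples cover all five domains and leave no domain undescribed.

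**Other sources can carry bad news.** This also stands. A reader might infer that the whole qualitative arm can hardly return a null or negative answer, or cannot tell cycle 2 what to fix. The document does not support that: debriefing feedback, the rubric, faculty evaluation and the expert panel are all inputs, and the report is never called the main source. These sources are only a partial substitute. A low rubric score does not say which teaching element failed. One rubric domain scores the group's shared reflection after practice; if that is the debriefing, which the article does not say, criticism would be voiced in a scored setting.

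**A reader might also infer that most topics presuppose benefit.** The text supports two of five.

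**Rigor safeguards exist.** The article plans reflexive journals, a coding record, peer debriefing, member reflections, an external audit and independent coding of a subset. These act on how material is interpreted. They cannot supply accounts that were not asked for, and no search for disconfirming accounts is among the safeguards described.

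**Counting students per theme is not part of the reflexive approach chosen.** Agreed. Disconfirming accounts can be reported by cycle without any claim about prevalence.

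**Conclusion.** The point holds in a limited form. As described, the individual reflective report leans toward benefit: two of five topics presuppose a gain, three are neutral and none invites an account of no help, no change or needed alteration. The consequence is greatest for students' own view of their crisis management, which the AEIS does not cover. Separately, the Methods state favourable comments and effects before the planned analysis.

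The conclusion assumes that the described topics reflect the questions fairly. If the full instrument already holds an open question on difficulties, the first part falls away and only the result-like sentences remain. The document gives no basis for putting a number on the distortion or on how many students saw no benefit.

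**What to change.** - Keep the five questions, so that reports stay comparable. Add one neutral question to the remaining cycle 1 reports and all cycle 2 reports: what did not help, was confusing or unpleasant, or did not change for you, and what should be altered?
- In the thematic analysis, plan a search for disconfirming and no-change accounts and report them by cycle.
- Remove the favourable statements from the Methods, or label them as preliminary cycle 1 impressions. No pilot is described, so genuine cycle 1 feedback should not be excluded from the dataset on this account.

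The cost is one short extra answer per report and some coding time. The answer will be missing from early cycle 1 reports, which should be stated when the cycles are compared. Cycle 2 enrols a new cohort, so the question can be complete there.
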